#### Engagement in teaching and learning activities

Following each of the three courses, we administer an instrument to assess students learning engagement in various domains. The importance of engagement beyond the cognitive domain to achieve significant learning has been described (67, 68). For example, connecting with fellow learners can raise confidence and contribute to more positive attitudes toward a course. This, in turn, can raise the emotional desire to learn, resulting in more time and effort being invested in engaging with learning materials, ultimately impacting learning outcomes (69–71). Some suggestive evidence for the link between engagement and empathy has been reported in the context of medical students’ learning communities (72). Researchers observed that valuing aspects of social, collaborative and behavioral engagement was associated with empathy. As such, engagement in one or more domains may impact the development of empathy.

We drew 12 items from the Online Student Engagement Scale (OSE) and made minor modifications for our purpose (73). The instrument will enquire about the following domains of learner engagement: behavioral and cognitive engagement (learning efforts-5 items), emotional engagement (interest and commitment-4 items), social and collaborative engagement (contributing and connecting-3 items). Students will assess how well certain behaviors, thoughts and feelings describe them in relation to each course on a 5-point Likert scale ranging from ‘describes me perfectly’ to ‘does not describe me at all’. An example item reads ‘Participating actively in group-project discussions.’ Validity and internal consistency (alpha = 0.91) of the OSE are satisfactory as assessed in university students in the United States.

#### Free-text items

During data collection following each of the three courses under investigation, we include an open-ended question inviting students to share how the courses have impacted their views and skills around patientcare. Survey questionnaires for Follow-ups 4–7 include the following open-ended question: ‘What makes a good healthcare professional, please describe’. Free-text responses are meant to provide some context to the quantitative findings.

### Sample size and data analysis—survey questionnaires

#### Sample size calculation

We conducted sample size calculations to estimate the number of participants required for an adequately powered analysis of the effect of the three courses under investigation on empathy as measured with the JSE-HPS. Considering a small effect size of 0.2 (20), a power of 80% and a two-tailed significance level of 0.05 we would need 199 participants at Follow-up 3. To account for an expected significant drop-out of >50% over time we aim to recruit 400 students into the study.

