### Participants

Participants in this study are freshmen dentistry, medicine, nursing, and pharmacy students at the National University of Singapore. There are no other inclusion criteria. All students enrolled in the respective programs will be invited to participate in this study (*n* = 900 per Academic Year). Participant Information Sheets are provided to all eligible students interested in joining the study. Students must provide consent before formally enrolling in each component of the research.

For the survey component, students will be enrolled in the study until their projected graduation. This means nursing, pharmacy and dentistry, and medical students will be enrolled for two to four, four, four and five years, respectively. For the interview component, a separate recruitment within the entire student cohort will be conducted, and consenting students will enroll for a single interview.

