#### Data analysis

To estimate the overall effect of the three courses on empathy and empathic care intentions across all students, we plan to conduct within-group t-tests. Repeated measures ANOVAs are planned to investigate the interactions between time and socio-demographic variables as well as engagement in teaching and learning activities on empathy and empathic care intentions. Significant interaction effects will be followed up with post-hoc tests and simple effects analysis as appropriate. Significant main effects will be followed up with post-hoc tests. The significance level will be set at 0.05. Data will also be plotted to visualize the results.

Free-text comments will be analyzed using qualitative thematic analysis (74). We will employ an inductive approach allowing the data to guide the generation of categories, themes and subthemes. We will first familiarize ourselves with the data by reading responses multiple times. Following this, we will conduct open coding of responses to capture all relevant content. We will then organize the codes into categories based on the overall topic they reflect. Within categories, we will identify themes and subthemes before crafting a narrative that will be supported by excerpts from the responses.

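### The target of 400 recruits covers a drop-out of at most 50.25% by Follow-up 3, although the plan expects more than 50%

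*Protocol article*

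**What the plan says.** In the protocol article, the section on sample size calculation sets its inputs as "Considering a small effect size of 0.2 (20), a power of 80% and a two-tailed significance level of 0.05" and concludes that "we would need 199 participants at Follow-up 3". The next sentence gives the recruitment target and its only justification: "To account for an expected significant drop-out of >50% over time we aim to recruit 400 students into the study".

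Three other places bear on this. The survey data analysis section states the test for the overall effect of the three courses: "we plan to conduct within-group t-tests". The section on survey data collection schedules surveys after each of Courses 1, 2 and 3 and then annually until graduation, so Follow-up 3 is not the last survey. The participants section says that "All students enrolled in the respective programs will be invited to participate in this study" and puts the pool at 900 per academic year.

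**The concern.** The requirement, the expected loss and the target stand in two consecutive sentences, and they do not fit together. A loss of more than half of 400 leaves fewer than 200 students, and the requirement is 199. Only a loss of exactly 201 students satisfies both the expectation and the requirement. A plan that expects more than 50% loss has therefore been sized for 50%.

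At stake is the claim that the analysis of the primary outcome is adequately powered. If loss by Follow-up 3 is well above one half, the chance of missing a true change of 0.2 is larger than the stated 20%, and a non-significant result could be read as evidence of no change when the study had become too small to show one.

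**Working it through.** **Inputs from the article.** Standardised effect 0.2, power 80%, two-sided significance level 0.05, 199 needed at Follow-up 3, drop-out above 50% with no upper value, recruitment aim 400 (all from the sample size section); within-group t-test (survey data analysis section); single group without a control (design section).

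**Input assumed here.** The effect of 0.2 is taken as the mean change divided by the standard deviation of the change, which is the scale a paired t-test uses. It reproduces the article's figure.

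**Step 1: reproduce 199.** The normal approximation is n = ((z for 0.975 + z for 0.80) / 0.2)² = ((1.960 + 0.842) / 0.2)² = 196.2, so 197. The exact calculation uses the noncentral t distribution with n − 1 degrees of freedom and noncentrality 0.2 × √n:

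- n = 198: power 79.97%
- n = 199: power 80.17%

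So 199 is the smallest number that reaches 80%. The article's figure is right and has no slack.

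**Step 2: reproduce 400.** Recruits needed = completers / (1 − d), where d is the drop-out. With d = 0.50, 199 / 0.50 = 398, which rounds up to 400. The target is therefore the allowance for a 50% loss.

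**Step 3: the largest loss that 400 can absorb.** 1 − 199/400 = 201/400 = 50.25%.

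**Step 4: what happens above that.** Completers = 400 × (1 − d). Power is the exact paired-t value at an effect of 0.2. The detectable change is the standardised change that gives 80% power with that many completers. Recruits needed = 199 / (1 − d), rounded up. Every loss above 50% in this table, other than the 50.25% limit from step 3, is an assumption, because the article gives no such figure.

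| Loss by Follow-up 3 | Completers from 400 | Power at 0.2 | Change detectable with 80% power | Recruits needed for 199 |
|---|---|---|---|---|
| 50% | 200 | 80.4% | 0.20 | 398 |
| 50.25% | 199 | 80.2% | 0.20 | 400 |
| 52% | 192 | 78.7% | 0.20 | 415 |
| 55% | 180 | 76.1% | 0.21 | 443 |
| 60% | 160 | 71.0% | 0.22 | 498 |
| 70% | 120 | 58.4% | 0.26 | 664 |

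Power falls more than 2 points below 80% from a loss of about 53% (188 completers, 77.9%).

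**The case against.** A reader might infer that 400 recruits fail to deliver 199 completers and that the stated 80% power is simply not met. The article does not support so flat a statement, for four reasons.

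- **No upper value.** The expected loss is given only as more than 50%. A loss of 50.25% satisfies that wording and still leaves 199, and up to about 52% the power stays within 2 points of 80%. The marked losses of power belong to drop-out rates that the article never states. This stands, and it makes the conclusion conditional.
- **Timing.** The 199 is needed at Follow-up 3, whereas the drop-out is described as occurring over time, and surveys continue to graduation. If the figure describes the whole follow-up, loss by Follow-up 3 could be lower and 400 could be enough. This reading is possible. It is the less natural one, because the sentence directly follows the Follow-up 3 requirement and is the only reason given for 400. It also leaves a gap: the article would then give no drop-out for the time point that it powers.
- **What the 80% refers to.** The article attaches 80% power to 199 participants at Follow-up 3, and that is correct. It does not say that 400 recruits secure 80% power at any drop-out.
- **An aim, not a cap.** Nothing says that recruitment stops at 400, and the invitation goes to the whole intake. Actual recruitment may exceed 400. This stands and makes the repair easy, but it does not make 400 the right allowance for the loss expected.

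It can also be said that the consequence is modest: at 60% loss the detectable change moves only from 0.20 to about 0.22. That is a fair argument against treating the point as critical.

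**Conclusion.** The concern holds in conditional form. The number of completers is right; the inflation is not matched to the stated expectation. The target of 400 absorbs a loss of at most 50.25%, so there is essentially no reserve. If the expected loss of more than 50% applies at Follow-up 3, power drops below 80% once that limit is passed.

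The size depends on a figure that the article does not give. Just above the limit the shortfall is negligible. At 60% loss, if that occurred, the chance of missing a true change of 0.2 would be 29% (100% − 71.0%) rather than 20%.

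The conclusion assumes that 0.2 is standardised by the standard deviation of the change, that the loss is counted at Follow-up 3, and that exactly 400 are recruited. This should be fixed because the article relies on the figure. It does not call the test, the outcome or the design into question.

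**What to change.** State the drop-out assumed at Follow-up 3, separately from any loss expected by graduation, and replace the current justification with wording such as:

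*400 recruits retain 80% power for a standardised change of 0.2 only if drop-out by Follow-up 3 is at most 50%; at 55%, 60% and 70% loss, power is about 76%, 71% and 58%, and the change detectable with 80% power is about 0.21, 0.22 and 0.26.*

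Describe 400 as a minimum. If the authors prefer to keep 80% power at a named loss d, set the target at 199 / (1 − d), for example 443 at 55% or 498 at 60%. Both are below the 900 students invited per academic year.

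The cost is one or two sentences in the sample size section and a slightly less favourable power statement. No added procedures are needed.

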#### Data analysis

To estimate the overall effect of the three courses on empathy and empathic care intentions across all students, we plan to conduct within-group t-tests. Repeated measures ANOVAs are planned to investigate the interactions between time and socio-demographic variables as well as engagement in teaching and learning activities on empathy and empathic care intentions. Significant interaction effects will be followed up with post-hoc tests and simple effects analysis as appropriate. Significant main effects will be followed up with post-hoc tests. The significance level will be set at 0.05. Data will also be plotted to visualize the results.

Free-text comments will be analyzed using qualitative thematic analysis (74). We will employ an inductive approach allowing the data to guide the generation of categories, themes and subthemes. We will first familiarize ourselves with the data by reading responses multiple times. Following this, we will conduct open coding of responses to capture all relevant content. We will then organize the codes into categories based on the overall topic they reflect. Within categories, we will identify themes and subthemes before crafting a narrative that will be supported by excerpts from the responses.

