### Design

This study is a longitudinal intervention study without a control group. We will use a mixed-methods approach, utilizing both quantitative and qualitative data to achieve our research objectives (43). Such an approach has been advocated for in healthcare education research (44). It is also warranted to account for the complexity of evaluating educational programs in general. Quantitative data will provide insights into the potential effects of the intervention on predefined outcomes (i.e., empathy), while qualitative research will provide context. Additionally, qualitative data can inform teaching practice of subsequent iterations of the Common Core Curriculum to improve the educational impact related to empathy.

The study began in August of 2023 with the first wave of recruitment and will run for 6 years. Data collection time points are scheduled along the duration of the study programs: between 2 and 5 years depending on the program. Figure 1 provides an overview of the study, including information on study enrolment, delivery of intervention courses, and data collection time points as well as data collection methods.

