### Data collection—survey questionnaire

Survey questionnaire data will be collected at baseline and at various other time points: following the conclusions of Courses 1, 2 and 3, and annually until student graduation. Students will self-administer the instruments through the online platform, Qualtrics.

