#### Empathy

The primary outcome of our study is cognitive empathy, as measured by the Jefferson Scale of Empathy, Healthcare Professions Student version (JSE-HPS). It appears to be the only available instrument designed specifically to measure empathy among healthcare professions students that is psychometrically sound (3). It is also the most commonly used instrument in this context (35). After conducting face and content validity assessments, the developers performed psychometric testing on a generic version intended for medical students. Using a sample of medical students, they established criterion validity, and the internal consistency was found to be desirable with a Cronbach’s alpha coefficient of 0.87 (56). Based on the generic version, three versions of the JSE were developed to allow administration in different populations: medical students, physicians and other healthcare professionals, and healthcare profession students. The psychometric properties of all versions were found to be reasonably comparable across locations (3). The JSE for medical students has been utilized in Singapore (34).

The JSE-HPS has been validated and used in students of various healthcare professions across geographical locations, including Asia (57–61). Students need to respond to 20 items using a 7-point Likert scale ranging from strongly disagree to strongly agree. To ensure the validity of responses, half of these items are negatively worded. The instrument measures three factors related to cognitive empathy: Perspective Taking-10 items, Compassionate Care-8 items, Standing in Patient’s Shoes-2 items. The JSE-HPS has been utilized in pharmacy students in Singapore (40).

To measure students’ intentions to provide empathic care, we drew from two existing instruments. First, the 12-item Reynolds Empathy Scale was developed in the United Kingdom for the nursing context (62). Scale development was based on patients’ perceptions of nurses’ behaviors that are helpful and unhelpful in showing empathy. Validity and reliability has been examined in terms of encounters with nurses (63, 64). Second, the 10-item CARE measure was developed to allow patients to assess their healthcare professionals’ empathic engagement (65, 66). The validity and internal consistency have been established in the United Kingdom (for medical doctors) by the developers of the instrument (66).

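### The course effect is to be tested with within-group t-tests on students who still answer at Follow-up 3, although more than half are expected to drop out and the intermediate surveys could be used

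*Protocol article*

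**What the plan says.** The Data analysis section for the survey names the method for the main aim: "To estimate the overall effect of the three courses on empathy and empathic care intentions across all students, we plan to conduct within-group t-tests". The Empathy section makes the JSE-HPS score the primary outcome. Repeated measures ANOVAs are planned for interactions of time with socio-demographic variables and engagement.

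The Sample size calculation section asks for 199 participants at Follow-up 3: "Considering a small effect size of 0.2 (20), a power of 80% and a two-tailed significance level of 0.05". It then deals with loss in one sentence: "To account for an expected significant drop-out of >50% over time we aim to recruit 400 students into the study".

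Surveys are taken at baseline and "following the conclusions of Courses 1, 2 and 3, and annually until student graduation". The first three follow-ups are therefore the post-course surveys, and students who leave before Follow-up 3 may already have given one, two or three scores. The baseline survey also records course of study, gender, age, ethnicity and housing type. The Design section states: "This study is a longitudinal intervention study without a control group".

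**The concern.** A within-group t-test of Follow-up 3 against baseline needs a pair of scores from each student. Anyone without a Follow-up 3 score contributes nothing, however many earlier surveys they completed. With more than half expected to be lost, the estimate describes those who kept answering a voluntary survey about empathy.

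That is harmless if those who leave would have changed, on average, as much as those who stay. If not, the difference goes straight into the estimated course effect, and with no control group there is no comparator in which a similar loss might offset it. Enrolling 400 instead of 199 keeps the number of pairs up but leaves this bias as it was. The repeated measures ANOVA in its standard form also drops incomplete cases, so it does not help.

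**Working it through.** **1. The plan's own figure.** Inputs from the Sample size calculation section: standardised effect 0.2, two-sided alpha 0.05, power 80%. For a paired t-test with the noncentral t distribution, power is 0.7997 at n = 198 and 0.802 at n = 199. So 199 reproduces, as a number of complete pairs with 0.2 in SDs of the change. (A two-group comparison would need 393 per arm.) Allowing for 50% loss, 199 / 0.50 = 398, rounded to 400. The study is sized on completers.

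**2. Bias as an identity.** With drop-out share q,

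bias = q x (mean change in completers - mean change in drop-outs).

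The gap is not in the documents and has to be assumed. At q = 0.50, with 199 completers and no mean change over all enrolled:

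| Assumed gap (SD of change) | Bias | Chance that the t-test is significant |
|---|---|---|
| 0.1 | 0.05 | 11% |
| 0.2 | 0.10 | 29% |
| 0.3 | 0.15 | 56% |
| 0.4 | 0.20 | 80% |

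**3. What could produce such gaps.** Simulation with 400 enrolled, drop-out of about 20%, 20% and 22% at the three follow-ups (about half left at Follow-up 3), true change zero, and 2,000 datasets per scenario. Assumptions: between-wave correlations 0.50 to 0.65 and drop-out log-odds of 0.4 to 0.7 per SD, with lower scorers or smaller gainers leaving. The likelihood analysis uses all four waves. Results are in baseline SDs. When the baseline to Follow-up 3 correlation is 0.50, the SD of change is sqrt(2 x (1 - 0.50)) = 1, so they compare directly with the planned 0.2. At 0.65 the SD of change is sqrt(2 x 0.35) = 0.84.

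| Drop-out depends on | Bias, completer t-test | Bias, likelihood analysis of all waves |
|---|---|---|
| nothing (random) | none | none; SE about 8% smaller (0.064 v 0.070) |
| baseline score | -0.08 to -0.20 | at most 0.002 |
| change seen so far | +0.06 to +0.15 | at most 0.002 |
| stable or unseen current empathy | 0.00 to +0.07 | +0.05 to +0.15 |

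In the second row, low scorers leave, those who stay start high and regress towards the mean, and a false decline appears. With a baseline to Follow-up 3 correlation of 0.50, the t-test rejects in about 38% to 78% of runs in that row and 23% to 52% in the third, where 5% is intended.

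**4. The last row.** If drop-out depends on a stable trait, the trait cancels from each student's change score. The completer t-test then has bias of at most 0.004 SD and rejects in 5% to 6% of runs. The likelihood analysis conditions on noisy observed scores and is biased by +0.04 to +0.11 SD, towards a false benefit. If drop-out depends on the unseen current score, both are biased, the likelihood analysis more.

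**The case against.** The strongest objection is that the t-test is sometimes the better method. A reader might infer that it is valid only if drop-out is unrelated to empathy altogether (missing completely at random). That is too strong: it needs drop-out unrelated to the change, and loss that depends on a student's stable level leaves it unbiased while the mixed model is not. This stands, and it is why the t-test should be kept beside the model.

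A reader might also infer a bias as large as the planned effect. The documents give no such figure. At 50% loss it needs an assumed gap of 0.2 / 0.50 = 0.40 SD between completers and drop-outs (0.2 / 0.70 = 0.29 even at 70% loss), which is the upper end of the scenarios. The largest simulated figures are false declines, which work against a claim that the courses help.

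A third tempting argument is that about 200 completers out of roughly 900 invited per year cannot stand for the student body. Most of that shortfall is students who never enrol, and no model of enrolled students addresses them.

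The article is condensed, and handling of missing data may be in a plan that is not shown. That stands for imputation and sensitivity analyses, whose absence is not the point here. The point is the method the article does fix, set against the loss it expects.

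Two readings of the wording are open. The phrase about all students may mean pooled over the four programmes, but a pooled estimate is still not meant to be confined to those who kept answering. The drop-out figure may cover the whole follow-up, but the article applies it to the number needed at Follow-up 3.

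Finally, without a control group neither analysis isolates a curriculum effect. True, but that is no reason to add an avoidable source of error.

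**Conclusion.** The concern holds in a limited form. The article fixes a method that, on observed data, uses completers only. It expects more than half the sample to be lost, and its only stated response is a larger intake, which does not touch bias. Under assumed drop-out driven by observed scores, the estimate is off by roughly -0.20 to +0.15 SD, against a planned effect of 0.2, and the sign depends on who leaves. A likelihood analysis of all waves removes that part and has about an 8% smaller SE under random loss.

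The sizes rest on assumed correlations and drop-out strengths, not on figures in the documents. The mixed model is not better in every case: it relies on data missing at random. When loss depends on stable or unseen empathy, it is off by +0.05 to +0.15 SD against 0.00 to +0.07 for the t-test. Neither analysis alone is enough.

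**What to change.** Before Follow-up 3 data are analysed, restate the main analysis of the JSE-HPS, and likewise of intentions, as a likelihood-based mixed model:

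- data: baseline and Follow-ups 1 to 3 from every enrolled student, including those who leave;
- time as a category, with unstructured covariance;
- programme and baseline demographics as covariates;
- main contrast: Follow-up 3 minus baseline.

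Report the completer paired t-test beside it, stating that it assumes drop-out unrelated to change. Add a delta-adjusted missing-not-at-random analysis that shifts the unseen Follow-up 3 scores over a stated range. If the model and the t-test disagree, say which drop-out assumption separates them.

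The cost is analysis wording and modest programming, with no new data. The downsides are slightly more complex reporting and an added missing-at-random assumption. The change does nothing for students who never enrol.

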The research is also limited by the fact that the available scientific literature on empathy interventions in healthcare professions students is primarily from high-income countries in North America and Europe (35). Relevant research from Asia is notably scarce, with a recent review (20) identifying only one such study, conducted in China (37). A later review focusing on qualitative aspects of empathy education interventions (38) identified another study, also from China (39). We are aware of only one relevant intervention study conducted in Singapore; this work involved an evaluation of a short empathy-training course for pharmacy students (40).

Lastly, intervention studies are typically conducted in students from a single healthcare discipline (20, 22, 36, 38). For instance, Winter’s review (2020) identified only one study that included healthcare students from multiple disciplines (41). Relatedly, most studies focused on medical and nursing students, with less research on pharmacy students and very little on dental students (42).

We responded to the call for mixed-methods longitudinal intervention research on empathy in healthcare professions students (3, 6, 35) and conceived a study recruiting freshmen dentistry, medicine, nursing and pharmacy students at the National University of Singapore. The primary aim of our study is to examine the effects of consecutive courses of a novel Common Core Curriculum for healthcare professions students that emphasize understanding patients, communication, and other critical areas of professionalism on empathy. Our secondary aims are: (a) Examining the effects of the novel curriculum on intentions to provide empathic care, (b) Studying the association between engagement in courses of the novel Common Core Curriculum and empathy as well as intentions to provide empathy care, (c) Exploring perspectives on and experiences with courses of the new Common Curriculum in relation to empathy and patientcare, and (d) Examining trajectories of empathy and intentions to provide empathy care beyond the novel Common Core Curriculum.

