#### Demographic information

At baseline, we collect the following demographic information from study participants: course of study, gender (male, female, other), age in years, ethnicity (Chinese, Indian, Malay, Other), and housing type as a proxy for socio-economic status of the family (private property or large government housing unit, to medium size government housing unit, small-size government housing unit).

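### Repeated-measures ANOVA is a poor fit for survey waves with over 50% expected drop-out and programme-dependent follow-up; a linear mixed model should replace it

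*Protocol article*

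**What the plan says.** All references are to the protocol article.

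- **Method.** Under Sample size and data analysis—survey questionnaires, Data analysis: "Repeated measures ANOVAs are planned to investigate the interactions between time and socio-demographic variables", with engagement in the courses as a further interaction variable. The outcomes are empathy and empathic care intentions. The waves that enter are not stated. The overall effect of the three courses is tested separately, with within-group t-tests.
- **Programme as a factor.** Under Demographic information: "we collect the following demographic information from study participants: course of study, gender" and others. Programme is therefore among the time interactions.
- **Waves.** Under Data collection—survey questionnaire, surveys follow baseline "following the conclusions of Courses 1, 2 and 3, and annually until student graduation". Under Free-text items: "Survey questionnaires for Follow-ups 4–7 include the following open-ended question". That makes up to eight waves including baseline.
- **Length of follow-up.** Under Participants: "nursing, pharmacy and dentistry, and medical students will be enrolled for two to four, four, four and five years, respectively". Design agrees that data collection spans "between 2 and 5 years depending on the program".
- **Aim.** Secondary aim (d) in the Introduction is "Examining trajectories of empathy and intentions to provide empathy care beyond the novel Common Core Curriculum".
- **Attrition.** Sample size calculation requires 199 students at Follow-up 3, expects drop-out above 50%, and sets recruitment at 400.

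**The concern.** Classical repeated-measures ANOVA needs a complete row for each student over the waves it covers. Two features of this study work against that. First, the plan itself expects to lose more than half of its students, and under this method the answers that leavers gave before leaving are discarded too. Second, students in shorter programmes are never surveyed at the later waves, so a longer window excludes them by design and not by chance.

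At stake are the programme-by-time and engagement-by-time results and, if the same method is used for it, the post-curriculum trajectory. Within the curriculum window the cost is lost precision and results for completers, who may differ from those who left. Beyond it, the analysis would cover fewer and fewer programmes, in a study whose Introduction stresses the inclusion of several professions.

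**Working it through.** **1. The plan's own figures.** Inputs from Sample size calculation: standardised effect 0.2, power 80%, two-sided 0.05. For a paired t-test the normal approximation is ((1.960 + 0.842)/0.2)² ≈ 196.2, so 197. The exact noncentral t calculation gives 199 (power 0.802), which is the stated number. Allowing for 50% loss, 199/(1 − 0.50) = 398, consistent with a target of 400. The largest loss that still leaves 199 of 400 is 1 − 199/400 = 50.25%.

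**2. Baseline to Follow-up 3.** On the plan's expectation at most about 199 of 400 students (49.75%) have Follow-up 3 data. A complete-case ANOVA also needs Follow-ups 1 and 2, so 199 is an upper limit. The loss here is attrition. All programmes take the three courses, so every programme has every wave and programme-by-time is estimable.

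**3. Later waves.** Assumption, because Figure 1 is not shown: Follow-ups 4 to 7 fall at the ends of years 2 to 5. Each programme's last wave is then Follow-up 4 (two-year nursing), 5 (three-year nursing), 6 (four-year nursing, pharmacy, dentistry) or 7 (medicine). Counting programme-by-wave cells with nursing split by length (six groups):

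| Window from baseline to | Cells | Empty by design | Groups with every wave |
|---|---|---|---|
| Follow-up 3 | 6 × 4 = 24 | 0 | all |
| Follow-up 4 | 6 × 5 = 30 | 0 | all |
| Follow-up 5 | 6 × 6 = 36 | 1 | all but two-year nursing |
| Follow-up 6 | 6 × 7 = 42 | 2 + 1 = 3 | four-year nursing, pharmacy, dentistry, medicine |
| Follow-up 7 | 6 × 8 = 48 | 3 + 2 + 1 + 1 + 1 = 8 | medicine only |

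If nursing is kept as one group, the only empty cells are the 3 of 4 × 8 = 32 at Follow-up 7. Two- and three-year nursing students would still be deleted from any window that outlasts them.

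**4. Complete cases in the longer windows.** The programme mix is not given. Assumed ranges: medicine 20%–70% of the sample, two- and three-year nursing 10%–50%.

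- 199 retained at Follow-up 3 and no later loss: to Follow-up 6, 199 × 0.5 to 199 × 0.9 = 100 to 179; to Follow-up 7, 199 × 0.2 to 199 × 0.7 = 40 to 139.
- With a further 10%–20% lost per year: to Follow-up 6, 199 × 0.5 × 0.8³ to 199 × 0.9 × 0.9³ = 51 to 131; to Follow-up 7, 199 × 0.2 × 0.8⁴ to 199 × 0.7 × 0.9⁴ = 16 to 91.
- Programme length alone, with no drop-out: to Follow-up 6, 400 × 0.5 to 400 × 0.9 = 200 to 360; to Follow-up 7, 400 × 0.2 to 400 × 0.7 = 80 to 280.

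The last line separates the two causes. Programme length by itself removes more than half of the sample only in the Follow-up 7 window, and only if medicine is less than half of it.

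**The case against.** The strongest reply is that no ANOVA over all eight waves is written down. The neighbouring text points to the curriculum window: the preceding sentence concerns the three courses, the sample size is set at Follow-up 3, and engagement is collected only around the courses ("Following each of the three courses, we administer an instrument to assess students learning engagement"). In that window every programme has every wave. The article is also a condensed account, so the waves in each model and the detailed method for a secondary aim may stand in a fuller document.

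Much of this stands, and it rules out several stronger readings that a reader might infer:

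- That the long-term trajectory, run as written, would describe medical students only. The waves are not stated, so this holds only if the ANOVA reaches Follow-up 7.
- That unequal programme length drops most students. The mix is not given, and the no-drop-out counts above do not show it.
- That aim (d) has no analysis. The article names no other longitudinal model for it, but that silence is not a finding.
- That the headline result is at risk. The within-group t-tests of the overall course effect do not depend on programme length.
- That unequal spacing of waves invalidates the ANOVA. Spacing alone does not break sphericity, and standard corrections exist.

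What the reply does not remove is that a specific method is named, and that it discards partial records in a study expecting to lose over half its students. That cost applies even on the narrow reading.

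**Conclusion.** The point holds as a moderate-priority improvement to secondary analyses. For baseline to Follow-up 3, classical repeated-measures ANOVA would use at most about 199 of 400 students; its interactions are estimable but rest on completers. If it is carried into the later annual waves it becomes unsuitable: gaps by design begin at about Follow-up 5, and to Follow-up 7 programme-by-time cannot be estimated because only medicine has data.

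The figure of 199 rests on the plan's own numbers and on the classical, complete-case form of the method. The onset of gaps rests on the inferred schedule. The complete-case ranges for later windows rest on an assumed programme mix and illustrate scale only.

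**What to change.** In Data analysis, replace repeated-measures ANOVA with a linear mixed model on all available observations: categorical time, programme, programme-by-time, the other socio-demographic or engagement terms with their time interactions, and within-student correlation. In addition:

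- State which waves enter each analysis.
- Treat waves after graduation as not applicable, not as missing.
- Estimate post-curriculum change for each programme over its own scheduled waves.
- Limit between-programme comparisons and pooled trajectory statements to waves that the programmes share. A mixed model keeps partial records but cannot fill a cell in which no one was surveyed.

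The cost is a change of wording and slightly more analysis work, with no new data. The model relies on data being missing at random given what is observed. That is an assumption to state, but it is weaker than the one needed for completers to represent everyone.
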